**Methods:**

This is a prospective, randomized, double-blind, placebo-controlled, multicenter trial with an estimated sample size of 306 cases, starting in January 2018. Patients aged 18 to 74 years, presented with a symptomatic anterior circulation occlusion with a deficit on the NIHSS of 4 to 25 points and treated with intravenous rtPA within the first 4.5 h of their clinical onsets, are eligible for participation in this study. The target time from the onset of symptoms to receive the study drug is of 10 h. Subjects are randomized 1: 1 to receive glibenclamide or placebo with a loading dose of 1.25 mg, followed by 0.625 mg every 8 h for total 5 days. The primary efficacy endpoint is 90-day good outcome, measured as modified Rankin Scale of 0 to 2. Safety outcomes are all-cause 30-day mortality and early neurological deterioration, with a focus on cardiac- and glucose-related serious adverse events.

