### Patient inclusion and exclusion criteria

Eligibility criteria are presented in Table 1. Patients aged 18 to 74 years with AIS and a symptomatic anterior circulation occlusion with a deficit on the National Institute of Health Stroke Scale (NIHSS) of 4 to 25 points, treated with intravenous rtPA within the first 4.5 h of clinical onset, are eligible for participation in this trial. The exclusion criteria are modified from that set in the previous study [15]. The diagnosis of AIS is based on cranial CT scan and clinical manifestations. However, since not all patients will receive brain MRI examination or angiography before randomization, the diagnosis of anterior circulation AIS will base largely on clinical symptoms and signs, and thus some patients with posterior circulation occlusion alone may be mistakenly included before an MRI examination or angiography done. Therefore, once these subjects are diagnosed with posterior circulation occlusion alone after being included, they would stop using the study drugs immediately, but continue to receive other standard treatment and follow-up. These participants will be excluded from the modified intent-to-treat population when performing statistical analysis. Site investigators are responsible for enrolling participants, obtaining informed consent and managing randomization.

**Table 1 Tab1:** Inclusion and exclusion criteria for the SE-GRACE trial

Criteria	Description
Inclusion criteria	1. Clinical diagnosis of acute ischemic stroke in the MCA territory (PCA and/or ACA territory involvement in addition to primary MCA territory stroke is acceptable)
	2. Aged ≥18 and ≤ 74 years
	3. A baseline NIHSS score between 4 to 25
	4. Intravenous rt-PA thrombolysis conducted within 4.5 h after stroke onset, if known, or the time last seen well [termed “time last known at neurologic baseline” (TLK@B)]
	5. The time to the start of administration of Study Drug must be ≤10 h after time of symptom onset or TLK@B
	6. Informed consent was signed by the subject or the legal representative
Exclusion criteria	1. Prior to stroke, significant disability exist, with modified Rankin Scale > 1 point
	2. With medical history or evidence of cerebral hemorrhage, subarachnoid hemorrhage, arteriovenous malformation, cerebral aneurysm or brain tumor
	3. With clinical or imaging evidence of contralateral cerebral infarction which is believed to have influence on the patient outcome by the investigators

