### Treatment

An overview of the study flowchart is presented in Fig. 1. Intravenous rtPA treatment will be initiated at a standard dose and regimen (0.9 mg/kg, initial bolus of 10% of the total dose and the remaining dose as an intravenous infusion lasting over 60 min) following current clinical guidelines [14]. When a patient meets all the inclusion/exclusion criteria and signs the informed consent, randomization will be performed and the study drug will be given as soon as possible after starting the infusion of rtPA treatment. Based on previous studies, the target time from symptom onset to the start of study drug is ≤10 h [9, 15]. The study drug (glibenclamide/placebo, 2.5 mg/pill) will be evenly divided with a pill splitter and given orally by trained hospital nurses. If the patient is unable to ingest orally due to dysphagia or altered consciousness, the study drug will be grinded and dissolved with water and administered through a nasogastric tube, followed by flushing down the nasogastric tube with water. In order to achieve a steady-state concentration rapidly, a loading dose of 1.25 mg will be given, followed by 0.625 mg every 8 h for 5 days. The total given dose will be 10 mg. Since the optimal dosage of oral glibenclamide in treating AIS remains unclear, in this study we use a relatively low-dose regimen differed from that of intravenous preparations [16], with combined consideration of its high bioavailability and hypoglycemic potency. In our preliminary study, the current dose regimen of oral glibenclamide was well tolerated, associated with less brain edema, and did not increase the risks of early death, hypoglycemia, and early neurological deterioration [17]. In addition, our unpublished data has shown that this dosing regimen was able to result in average steady-state plasma glibenclamide levels of 19 ng/mL, which is not inferior to the concentrations reached by the effective therapeutic dose in rats [16].

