**Fig. 1 Fig1:**
[figure not shown]
Flowchart of the trial. AIS, acute ischemic stroke; SAEs, severe adverse events; IQCODE, Informant Questionnaire on Cognitive Decline in the Elderly. *If a patient is discharged within 7 days, the examination will be performed at the day of discharge

To increase the adherence to intervention protocols, all participants will receive their study drugs at the scheduled time and take the medicine under the supervision of trained nurses. Because all subjects will receive thrombolytic therapy, for safety reasons, these patients will be hospitalized for minimum of 5 days to monitor the changes in their conditions with their complete examinations such as stroke etiology and vascular status. These all will be undertaken unless the patients voluntarily request discharge or death occurs. The patients who ask to be released from the hospital within 5 days will no longer be treated with the study drugs but will be included in the modified intent-to-treat population.

Neurological statue presented as NIHSS scores will be assessed at enrollment and at 24, 48, 72 h and 7 days. Electrocardiograms will be obtained at baseline, 6 h after the study drug administration, and at 7 days. Vital signs will be monitored frequently during the period of study drug administration. Safety lab values will be assessed at enrollment and at 24, 48, 72 h and 7 days. Cranial CT examination will be performed before randomization and repeated at 24 h, 72 to 96 h, and as clinical indicated. If a participant is discharged within 7 days, the examination will be performed at the day of discharge instead.

Since glibenclamide is an active hypoglycemic agent, blood glucose levels will be checked every 2 h during the first 24 h, followed by every 4 h in the absence of any decline below 3.9 mmol/L during the period of study drug administration. In the case of hypoglycemia, blood glucose level will be corrected by administration of glucose or glucagon, as appropriate. For safety reason, if two consecutive events of hypoglycemia (< 3.9 mmol/L) or one incidence of serious hypoglycemia (< 2.2 mmol/L) occurs, the study drug will be suspended. Blood glucose and corrective glucose administration will be reported.

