### Outcome assessments

All patients will be followed up by trained neurologists blinded to study data. The primary and secondary endpoints of this study are summarized in Table 2. The SE-GRACE trial is designed with combination of clinical, imaging and biochemical outcomes to provide information about clinical benefits and relevant mechanism of action. Subjects will be followed up in person or through telephone review at 30 ± 7 days, 90 ± 14 days (the primary end-point), 180 ± 30 days and 360 ± 30 days after the onset of AIS, using modified Rankin Scale (mRS), Barthel Index (BI) and Informant Questionnaire on Cognitive Decline in the Elderly (IQCODE) (Fig. 1) [21, 22]. The primary outcome will compare the proportion of “good outcome” in the glibenclamide-treated group to the placebo group, with good outcome defined as a patient with a mRS of 0–2 at 90 days after the onset. The BI is a 10-item measure of activities of daily living which is frequently used in clinical practice and as a trial outcome measure in stroke, with a total score of 60 to 100 generally regarded as good outcome [23]. The IQCODE is an informant-based assessment tool for diagnosis of poststroke dementia and/or multidomain cognitive impairment, with a pooled sensitivity of 0.81 and specificity of 0.83 in a recent a systematic review [22]. The cutoff value of IQCODE for diagnosing poststroke dementia is generally considered to be > 3.4 [21, 22].

**Table 2 Tab2:** Primary and secondary endpoints of the trial

Outcome	Description
Primary outcome	The ratio of mRS ≤ 2 at 90 days after the stroke onset
Secondary outcome	1. The ratio of NIHSS decreased ≥4 points at 7 days after the stroke onset
	2. The ratio of parenchymal hemorrhagic transformation in cranial CT within 96 h after the onset
	3. The ratio of midline shift ≥6 mm in cranial CT within 96 h after the onset
	4. The mRS shift at 90 days after the onset
	5. The ratio of Barthel Index of 60–100 points at 90 days after the onset
	6. The proportion of Informant Questionnaire on Cognitive Decline in the Elderly (IQCODE) of ≤3.40 at 6 months and 1 year after the stroke onset
	7. The serum concentration of MMP-9 at baseline, and at 24, 48, and 72 h after onset
Safety outcome	1. The mortality at 90 days after the onset
	2. The ratio of neurological deterioration (NIHSS increased ≥4 points) within 24 h after the onset
	3. The incidence of hypoglycemia (random blood glucose < 3.9 mmol/L)

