	4. The incidence of cardiac events in cardiac examination (ECG, echocardiography)
	5. The incidence of pulmonary infection
	6. The incidence of adverse event and serious adverse event

In terms of cranial CT, parenchymal hemorrhagic transformation (PH) including PH1 type and PH2 type are defined as hematoma with some space-occupying effect [24], which has been considered as a bad prognostic sign [25]. Midline shift will be measured in the section of third ventricle and categorized at 6 mm. The serum concentration of matrix metalloproteinase-9 (MMP-9) will be measured at baseline, and at 24, 48, and 72 h after the stroke onset to reflect the integrity of the blood-brain barrier [15].

Since the study will recruit AIS with NIHSS scores of 4 to 25 who are treated with intravenous rtPA, most of the included patients are severely ill and thereby most adverse events (AE) are common in this patient group irrespective of treatment strategies. AEs will be recorded on daily basis. AEs relevant to the study drug are considered to be the need for decompressive craniectomy (determined by neurosurgeons) and hypoglycemia < 3.9 mmol/L in the first 5 days. All-cause mortality, cardiac mortality, early neurological deterioration (NIHSS increased ≥4 points within 24 h of the onset) and cardiac-related and blood glucose-related AEs/SAEs will be of specific focus.

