### Statistical analyses

The primary outcome will be compared between 2 groups using χ^2^ tests, and the confidence interval of the rate difference will be calculated using the Newcombe’s method [27]. Common risk difference for multiway 2 × 2 tables stratified by endovascular treatment and baseline NIHSS score (≥ 14 or < 14) will also be reported. The Mantel-Haenszel estimate, confidence limits, and test for the common risk differences by using Mantel-Haenszel stratum weights and the Sato variance estimator will be used. When half of the planned subjects are recruited and their 90-day follow up are finished, interim analysis will be conducted by a selected biostatistician. O’Brien - Fleming method will be used to control the Type I error. The trial will be stopped early when the primary outcome of the interim analysis significantly favors or contradicts the usage of glibenclamide.

For baseline variables and other outcomes, comparisons between normally distributed continuous variables, expressed as mean ± SD, will be performed using 2-sample t tests; non-normally distributed continuous variables, presented as median and interquartile range, will be analyzed using Wilcoxon rank sum tests. Pearson χ^2^ or Fisher exact tests will be used, as appropriate, for categorical data, which will be expressed as percentages. For secondary outcomes mRS shift and MMP-9, mixed effect model will also be used.

For safety analysis, all adverse events and serious adverse events, including deaths, will be summarized by body systems in terms of frequency, severity, and relatedness to the study drug using the MedDRA codes. Frequencies of adverse events from these two groups will be reported. Pearson χ^2^ or Fisher exact tests will be used, as appropriate, to compare the incidence of adverse events between the two groups.

Subgroups analyses will be performed according to pre-defined design variables, such as: sex, age (≤ 60 years vs. 61–74 years), endovascular treatment, NIHSS grade (4–13 vs. 14–25), time window in rtPA thrombolysis (< 3.5 h vs. 3.5–4.5 h), and study drug treatment time (< 6 h vs. 6–10 h).

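### Early neurological deterioration is counted only to 24 h after stroke onset, so this safety outcome covers roughly one-eighth to one-sixth of the five-day dosing period

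*Protocol article*

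**What the plan says.** Table 2, safety outcome 2, is "The ratio of neurological deterioration (NIHSS increased ≥4 points) within 24 h after the onset". The text under Outcome assessments repeats the definition, "early neurological deterioration (NIHSS increased ≥4 points within 24 h of the onset", and lists it among the events to receive particular attention. The abstract gives it more weight still: "Safety outcomes are all-cause 30-day mortality and early neurological deterioration".

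On exposure, Table 1 (inclusion criterion 5) says "The time to the start of administration of Study Drug must be ≤10 h after time of symptom onset or TLK@B". The Treatment section says "the study drug will be given as soon as possible after starting the infusion of rtPA treatment" and, on duration, "a loading dose of 1.25 mg will be given, followed by 0.625 mg every 8 h for 5 days". Statistical analyses plans a subgroup by "study drug treatment time (< 6 h vs. 6–10 h", so the protocol itself expects start times to spread over the permitted range.

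On measurement, the Treatment section says that NIHSS "will be assessed at enrollment and at 24, 48, 72 h and 7 days". It does not say from what moment those hours run. The only other NIHSS outcome in Table 2 (secondary outcome 1) counts improvement of at least 4 points at 7 days.

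**The concern.** A safety outcome for a drug should watch patients while they are on it. This one starts its clock at stroke onset, before anyone has been dosed, and stops while most of the course is still to come. Two things follow.

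- Worsening between the enrolment score and the first dose counts as an event although the drug cannot have caused it. Such events should fall equally on both arms and so dilute a drug-related difference.
- Worsening after 24 h from onset, when most of the drug is given, does not count at all.

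Both make harm harder to see in an outcome that the abstract puts forward as evidence of safety. Exposure inside the window also differs between patients, because it depends on how soon after onset each was dosed.

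**Working it through.** **Plan's own figure.** The protocol gives no expected rate, power or sample size for this outcome; the 306 patients are sized on 90-day mRS. The check is therefore one of time windows.

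**Inputs**
- Window: 0 to 24 h after onset (Table 2; Outcome assessments).
- Latest first dose: 10 h after onset (Table 1).
- Dosing period: 5 days × 24 = 120 h (Treatment).
- Alternative length: the stated total of 10 mg implies (10 − 1.25) / 0.625 = 14 maintenance doses, so the last dose falls 14 × 8 = 112 h after the first.

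**Step 1: on-drug time inside the window.** Hours = 24 − start time; share = hours / dosing period.

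| First dose after onset | On-drug hours in window | Share of 120 h | Share of 112 h |
|---|---|---|---|
| 10 h | 14 | 11.7% | 12.5% |
| 6 h | 18 | 15.0% | 16.1% |
| 4.5 h | 19.5 | 16.3% | 17.4% |
| 0 h (impossible bound) | 24 | 20.0% | 21.4% |

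Starts before 4.5 h are possible if rtPA is given early, but no start can exceed the last row. On the 120 h basis, 88.3% of dosing time lies outside the window for a start at 10 h and 83.7% for a start at 4.5 h.

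**Step 2: time before the first dose.** A first dose at 10 h leaves 10 of the window's 24 h before any drug. Not all of this can yield an event: a rise needs a reference score, and the first scheduled one is at enrolment. Only the gap between enrolment and first dose matters, and the article gives no figure for it.

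**Step 3: what covers the later period.** Other outcomes run longer:
- Parenchymal haemorrhage and midline shift run to 96 h after onset. For a start at 10 h that is 96 − 10 = 86 h on drug, or 71.7% of 120 h.
- Hypoglycaemia as a drug-relevant event is followed for the first 5 days.
- NIHSS worsening stops at 24 h. The 48 h, 72 h and day-7 scores feed no outcome that detects worsening.

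**Step 4: what a first-dose clock would cover.**
- 24 h from first dose is 24 / 120 = 20% of dosing for every patient, so exposure is equal.
- 72 h from first dose is 72 / 120 = 60%.
- Day 7 (168 h) covers the whole course, which ends at the latest 10 + 120 = 130 h after onset.
- The scheduled 24 h score falls within 24 h of first dose whether it is timed from onset or from enrolment, since both precede the first dose.

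**The case against.** The strongest reply is that the outcome is labelled early, is defined identically in both places, and follows a form that allows comparison with other studies. It is not an internal contradiction, and that stands. The label explains a short window. It does not explain starting a drug-safety clock at onset.

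Second, late worsening is not invisible. Adverse events are recorded daily, adverse and serious adverse event incidence is a safety outcome, mortality is another, and an independent board reviews safety. A patient who is worse at day 7 also counts as a non-responder on secondary outcome 1. This stands too, and it limits the seriousness of the point. But none of these routes applies the 4-point NIHSS rule, and a non-responder count does not separate patients who worsened from those who merely failed to improve.

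Third, allocation is randomised and double-blind, so pre-dose events and unequal exposure affect both arms alike. That is correct: the consequence is dilution and loss of sensitivity, not bias between arms. Hours before the enrolment score add nothing, because no scheduled earlier score exists from which to measure a rise.

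**Conclusion.** The point holds as a badly placed window. For first doses between 10 h and 4.5 h after onset, the outcome covers about 12% to 16% of a 120 h dosing period, and it cannot exceed about 21% for any start on either measure of length. No listed outcome uses the later NIHSS scores to detect worsening. The result assumes a full five-day course and takes the definition as printed.

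Three stronger readings are tempting and are not supported.

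- A reader might infer that most deterioration on drug goes uncounted. The arithmetic gives a share of hours, not of events. The documents give no timing of deterioration; if events cluster early, the share missed is smaller than the share of time.
- A reader might infer that no scheduled on-drug NIHSS lies inside the window. That needs the 24 h visit to run from enrolment (enrolment at 6 h would put it at 30 h after onset). The text does not say so, and the 7-day NIHSS outcome, MMP-9, CT outcomes and follow-up visits are all timed from onset. On that clock the score falls at the window's edge and is on drug for every permitted start.
- A reader might infer that swelling-related harm escapes observation. It does not: CT is also done at 24 h, midline shift is an outcome to 96 h, and need for craniectomy is a named drug-relevant event.

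What remains is an inexpensive improvement to a prominent safety outcome that is worth making. It does not invalidate the trial's safety assessment.

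**What to change.** 1. Keep the 24 h-from-onset outcome, for comparison with other trials.
2. State whether the 24 h NIHSS visit is timed from onset, enrolment or first dose.
3. Add a safety outcome: NIHSS rise of at least 4 points from the last score before the first dose. Report it by arm within 24 h of first dose, and cumulatively through 72 h and through day 7.
4. Count deaths in each interval as deterioration or show them beside it, so that a patient who dies before the next score does not drop out of the table.

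**Cost.** One definition and one further safety tabulation from scores already scheduled; no new visit and no change to treatment or care. The added version is slightly less comparable with onset-based definitions, which is why the existing one stays. For patients discharged before day 7 the protocol takes the score on the day of discharge, so the day-7 table should say how many scores are of that kind.

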### Quality control and data monitoring

The Executive Committee (12 members, lead investigator - [name]) is responsible for the development of the study protocol and its amendments. The protocol is adapted to the ‘Standard Protocol Items: Recommendations for Interventional Trials’ (SPIRIT), and an additional file is added listing each paragraph and its location in the protocol (Additional file 2).

All investigators are “good clinical practice” (GCP) certified personnel and have participated in the training sessions to ensure that they fully understand the trial protocols and the standard procedures before the study. Other involved personnel (i.e. nurses) have been trained in their specific roles. Inspectors will be nominated to visit each study site regularly in order to monitor the implementation of the protocols and assess the compliance of the participants and investigators.

All data will be recorded in case report form (CRF) and entered into the Electronic Data Capture System by trained clinical research coordinators. To ensure confidentiality, CRFs will be identified with only initials and participation number rather than the participants’ real identities. Besides, all personal information collected from the enrolled participants will be stored by investigators of each hospital in a locked area. An Independent Data Safety Monitoring Board (IDSMB) including one neurologist, one biostatistician and one clinical pharmacologist will be assembled by the lead investigator, with responsibilities including but not limit to safeguard the interests of trial participants, assess the safety and efficacy of the interventions during the trial, monitor the overall conduct of the clinical trial, and provide recommendations about stopping or continuing the trial [26]. An independent biostatistician team selected by the members of IDSMB will perform the interim analysis and a ‘Formal Interim Analysis’ meeting will be held by the IDSMB to review data relating to the treatment efficacy, patient safety and quality of trial conduct. The IDSMB will let the study team know the final decision and the whole team has no access to the interim analysis result. The data managers and study biostatisticians will only access the data for its management and statistical analysis and will not be involved in the clinical management in any regards.

